### Assessments

An extensive baseline assessment is performed including questionnaires, measurement of physical activity, and clinical, laboratory, microbiological, and neuropsychological evaluation. Neurological symptoms are assessed by the lead study physicians using a standardized interview and clinical neurological examination at baseline and week 14 [25].

Study visits for safety evaluation are performed at week 2, week 8, and week 14 after baseline. Safety assessments include a medical history, physical examination, and laboratory investigation (hemoglobin, hematocrit, leukocytes, platelets, glucose, creatinin, alkaline phosphatase, alanine aminotransferase).

Efficacy evaluation is performed at week 14 (end of treatment period, EOT), week 26 (12 weeks after EOT), and week 40 after baseline (end of study, EOS, 26 weeks after EOT). After the last comprehensive outcome assessment at week 40, patients are surveyed by post-study questionnaires at week 52.

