### Statistical analysis

Data will be analyzed according to the modified intention-to-treat (mITT) principle. Patients who have been randomized into the study and received at least one dose of ceftriaxone are included in the mITT analysis group. In the primary analysis, analysis of covariance (ANCOVA) will be used to compare the three study arms, with gender and the baseline value of the dependent variable as covariates. Pairwise comparisons are performed for the different treatment modalities with Bonferroni correction for multiple comparisons. Missing data will be imputed by carrying the last observation forward, in order to obtain a conservative estimate of the treatment effect. No interim efficacy analysis will be performed. Two-sided 5% significance levels will be used to identify statistically significant results. All confidence intervals reported will be 95% confidence intervals. All statistical analyses will be performed using SPSS software.

A sensitivity analysis will be performed on the per-protocol subgroup. The per-protocol population comprises of patients for whom all of the following apply: has met the in- and exclusion criteria; has taken at least 75% of the study drugs as recorded by MEMS; has not taken any other antimicrobial drug for more than 5 days during the study period; has not taken any prohibited concomitant medication; has not been unblinded before end of study.

When a difference between one of the experimental treatments (ceftriaxone followed by 12 weeks of either of the oral treatments) and the reference treatment (two weeks ceftriaxone followed by placebo) is found, subgroup analyses will be performed to identify factors that may affect the treatment outcome. This will be done by adding the factors and their interaction with the treatment to the analysis of covariance model. The duration of treatment effect will be evaluated in an explorative way with linear mixed models. When an outcome variable is measured more than once, a random (patient-dependent) intercept will be included in the analysis.

To evaluate the neuropsychological outcomes, results on individual tests will be standardized into z-scores to make across-test comparison possible (using baseline group mean and standard deviation as reference), and averaged into cognitive domain scores. Higher z-scores reflect a better performance. If necessary, scales will be inverted, e.g., in the case of reaction times where higher scores reflect a slower performance.

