### Sample size

The final power calculation was based on a pilot study on 80 patients with borreliosis-attributed persistent symptoms ([name] et al., unpublished). Patients were classified as having a poor or reasonable clinical condition as assessed during the first clinical consultation at the outpatient clinic. The difference in the PCS score between patients with a poor and those with a reasonable clinical condition was 3 points, with a standard deviation of 8. This corresponds with the minimally clinically important difference (MCID) of 2 to 5 points that has been proposed for the PCS [46]. In order to detect a difference of 3 points with a power of 90%, a two-sided alpha of 5% and a reliability coefficient (correlation between consecutive measurements) of 0.7 [47], a minimum of 75 patients are required per treatment group (225 patients in total). To compensate for possible loss to follow-up, a study population of at least 255 patients is targeted for.

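### The duration-of-effect model names only a random patient intercept; fitted that way, it misstates the precision of change between visits if correlation falls with time

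*Protocol article*

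**What the plan says.** The Statistical analysis section of the protocol article separates two analyses. The primary one, at week 14, is an ANCOVA: "analysis of covariance (ANCOVA) will be used to compare the three study arms, with gender and the baseline value of the dependent variable as covariates". Durability is handled separately: "The duration of treatment effect will be evaluated in an explorative way with linear mixed models". The next sentence gives the treatment of repeated measurements: "When an outcome variable is measured more than once, a random (patient-dependent) intercept will be included in the analysis". No random slope, residual covariance or robust standard error is mentioned, and none is excluded.

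The Assessments section sets the visit schedule: "Efficacy evaluation is performed at week 14 (end of treatment period, EOT), week 26 (12 weeks after EOT), and week 40 after baseline". Post-study questionnaires follow at week 52. The efficacy visits are therefore 12, 14 and 26 weeks apart.

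The Sample size section gives the one correlation in the article, a "reliability coefficient (correlation between consecutive measurements) of 0.7". No value is given for a longer gap.

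**The concern.** A random intercept with independent residuals implies compound symmetry: one variance and one correlation for all pairs of visits. Weeks 14 and 40 are then treated as being as strongly correlated as weeks 14 and 26, although the gap is more than twice as long. If the true correlation weakens over the longer gap, the model applies an average correlation everywhere. It overstates the precision of the long-gap comparison and understates that of the short-gap ones.

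The long-gap comparison, whether the arms drift together or apart between the end of treatment and week 40, is one direct way to ask how long an effect lasts. Its confidence interval would be too narrow and its test would reject too often. The mixed model is the only analysis that the section names for duration of effect.

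**Working it through.** **Inputs from the article.** Efficacy visits at weeks 14, 26 and 40; SD 8 points; correlation 0.7 between consecutive measurements; 75 patients per group.

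**Inputs assumed.** Correlations at longer gaps, equal variances at all visits, complete data, and a model containing a random intercept and independent residuals only.

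**The plan's own figure.** The article states no figure for the mixed model. Its sample size is for week 14: a difference that "was 3 points, with a standard deviation of 8", 90% power and two-sided 5% alpha. ANCOVA gives 2 × (8/3)² × (1 − 0.7²) × (1.960 + 1.282)² = 76.2, so 77 per group against the stated 75, with power of 89.5% at 75. This is close enough to count as reproduced. The calculation does not involve the mixed model.

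**Standard error of the arm difference in change between two visits**, n per arm, pair correlation r, mean correlation over the three pairs r̄:

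- true SE = √[(2/n) × 2 × SD² × (1 − r)]
- model SE = √[(2/n) × 2 × SD² × (1 − r̄)]
- ratio (model/true) = √[(1 − r̄)/(1 − r)]
- actual rejection rate of a nominal 5% test = 2 × [1 − Φ(1.96 × ratio)]

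**Worked case.** Correlations 0.7 (weeks 14–26), 0.7 (26–40) and 0.5 (14–40) give r̄ = 1.9/3 = 0.633. With n = 75 and SD 8, the constant (2/75) × 2 × 64 is 3.413.

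- Weeks 14–40: true SE √(3.413 × 0.5) = 1.306; model SE √(3.413 × 0.367) = 1.119; ratio 0.856; rejection rate 9.3%.
- Weeks 14–26: true SE √(3.413 × 0.3) = 1.012; model SE 1.119; ratio 1.106; rejection rate 3.0%.

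**Range over assumed patterns:**

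| Correlations 14–26 / 26–40 / 14–40 | Ratio, weeks 14–40 | Actual level | Ratio, adjacent visits | Actual level |
|---|---|---|---|---|
| 0.7 / 0.7 / 0.7 | 1.000 | 5.0% | 1.000 | 5.0% |
| 0.7 / 0.7 / 0.65 | 0.951 | 6.2% | 1.027 | 4.4% |
| 0.7 / 0.7 / 0.6 | 0.913 | 7.4% | 1.054 | 3.9% |
| 0.7 / 0.7 / 0.5 | 0.856 | 9.3% | 1.106 | 3.0% |
| 0.8 / 0.8 / 0.6 | 0.816 | 11.0% | 1.155 | 2.4% |

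The ratios do not depend on n or SD. A simulation of 400 null trials in the 0.7/0.7/0.5 case, with 80 patients in each of two arms and a random-intercept REML fit, rejected in 9.0% (weeks 14–40) and 2.75% (weeks 14–26), in line with the formula.

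**Single-visit arm differences.** With equal variances and no baseline covariate, the SE at one visit rests on the total variance, so decaying correlation does not disturb it. If baseline enters with one common slope b and its correlation with later scores falls, some error returns. Take assumed baseline correlations of 0.7, 0.6 and 0.5 at weeks 14, 26 and 40. Then b = 0.6, and the residual variance (in SD² units) is 1 + b² − 2br, that is 0.52, 0.64 and 0.76, with mean 0.64. At week 40 the ratio is √(0.64/0.76) = 0.918 and the test runs at 7.2%. With 0.7, 0.65 and 0.6 it runs at 6.3%. With 0.7 per 14 weeks compounding (0.7, 0.516, 0.361) it runs at 7.8%.

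**The case against.** The strongest reply is that the article never calls the random intercept the sole covariance term. It says that one is included, and a random intercept can be combined with a structured residual covariance. Residual structure and visit coding are also details that an article often leaves to a full protocol or SAP, and neither is shown. It stands that a reader might infer an explicit commitment to independent residuals, which the text does not contain. It does not stand that the matter is simply left open. The article names one device, and an analyst who followed the sentence would fit that device. The point is a comment on a stated choice.

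The second reply is that the harm is conditional. This stands in full. A reader might infer that the standard errors will be wrong, but 0.7 between consecutive measurements is compatible with equal correlation, where the test holds its 5.0% level. Nothing in the article shows which pattern applies.

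The third reply is that duration of effect need not mean a week 14-to-40 change. It could mean whether the arms still differ at week 26 or week 40, and those contrasts are largely spared, subject to the baseline-adjustment effect shown above. A false positive on the change contrast would also mean wrongly concluding that the effect changed between visits. It would not mean wrongly claiming lasting benefit. Both observations stand and narrow the point.

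Finally, the analysis is declared exploratory, and no confirmatory claim rests on it. That limits the weight of the point, but the section promises 95% confidence intervals throughout, and exploratory intervals should also have about their stated coverage.

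**Conclusion.** The point holds in a conditional form and is minor. If the duration-of-effect model is fitted with the named random intercept and independent residuals, and if correlation falls with time, the standard error of the week 14-to-40 treatment difference in change is about 5% to 18% too small over the decaying patterns tried. The nominal 5% test then runs at 6.2% to 11.0%. Adjacent-visit standard errors are about 3% to 15% too large. Under equal correlation there is no error. These figures assume complete data and equal variances, and the decay patterns are illustrations, not values from the article.

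A reader might go further and infer that the trial's main result is at risk. The article does not support that: the week 14 comparison is an ANCOVA that does not use this model, and the sample size does not depend on it.

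**What to change.** Replace the random-intercept sentence, for the duration-of-effect analysis, with an unstructured covariance over the follow-up visits, visit as a categorical factor, and treatment-by-visit and baseline-by-visit terms. The unstructured matrix takes the place of the random intercept and is not added to it, since it already carries the between-patient variation.

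The matrix has 3 × 4/2 = 6 parameters for weeks 14, 26 and 40, or 4 × 5/2 = 10 if week 52 is included, against 2 for the random-intercept model. With a target of at least 255 patients, the extra parameters cost almost no precision. The baseline-by-visit term and the visit-specific variances also deal with the week 40 effect of baseline adjustment.

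The cost is a wording change and a different covariance option in the mixed-model procedure. No data collection, sample size or primary analysis changes. If a richer covariance was always intended, one clause stating it is enough.

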### Sample size

The final power calculation was based on a pilot study on 80 patients with borreliosis-attributed persistent symptoms ([name] et al., unpublished). Patients were classified as having a poor or reasonable clinical condition as assessed during the first clinical consultation at the outpatient clinic. The difference in the PCS score between patients with a poor and those with a reasonable clinical condition was 3 points, with a standard deviation of 8. This corresponds with the minimally clinically important difference (MCID) of 2 to 5 points that has been proposed for the PCS [46]. In order to detect a difference of 3 points with a power of 90%, a two-sided alpha of 5% and a reliability coefficient (correlation between consecutive measurements) of 0.7 [47], a minimum of 75 patients are required per treatment group (225 patients in total). To compensate for possible loss to follow-up, a study population of at least 255 patients is targeted for.

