## Methods/Design

### Study design

A randomized, double-blind, placebo-controlled trial is performed to determine whether long-term antibiotic treatment (ceftriaxone followed by doxycycline or ceftriaxone followed by the combination of clarithromycin and hydroxychloroquine) leads to better patient outcome than short-term treatment (ceftriaxone followed by placebo) in patients with borreliosis-attributed persistent symptoms. This prospective 3-arm study is conducted at two sites in the Netherlands, the Radboud university medical center (Radboudumc) and the Sint Maartenskliniek, and has been approved by the Medical Ethics Review Committee CMO Regio Arnhem-Nijmegen (registration number 2009/187, NL27344.091.09). The study is conducted in accordance with the principles stated in the most recent version of the Declaration of Helsinki and the International Conference on Harmonisation (ICH) guidelines on Good Clinical Practice.

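### The stated 90% power with 75 patients per arm ignores the Bonferroni correction used in the analysis; each experimental-versus-placebo comparison has about 79%

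*Protocol article*

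**What the plan says.** The Sample size section takes its target from a pilot study, where the PCS difference between patients in poor and in reasonable condition "was 3 points, with a standard deviation of 8". The specification reads: "In order to detect a difference of 3 points with a power of 90%, a two-sided alpha of 5"%. Baseline adjustment enters the calculation through an assumed "reliability coefficient (correlation between consecutive measurements) of 0.7". From these inputs the section concludes that "a minimum of 75 patients are required per treatment group (225 patients in total"). Enrolment is raised to at least 255, which is 85 per arm, to allow for loss to follow-up. The section mentions no adjustment for multiple comparisons.

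The Statistical analysis section compares the three arms by ANCOVA, with gender and the baseline value as covariates, and continues: "Pairwise comparisons are performed for the different treatment modalities with Bonferroni correction for multiple comparisons". It does not say how many comparisons the correction covers.

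The Study design section asks whether long-term treatment, with either oral regimen, "leads to better patient outcome than short-term treatment (ceftriaxone followed by placebo) in patients with borreliosis-attributed persistent symptoms".

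**The concern.** The alpha used to size the trial is not the alpha at which the comparisons of interest will be tested. With three arms there are three pairs, so Bonferroni puts each at 1.67%, while the sample size rests on 5%. One of the three shares goes to doxycycline versus clarithromycin–hydroxychloroquine, although the Study design section asks about each long regimen against placebo.

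This is more than detail left to a separate analysis plan. The article states both the sizing alpha and the corrected test, and they do not match. The mismatch matters because the Discussion expects the trial to support either prescribing or withholding prolonged antibiotics. A null result will be read against the advertised 90% power, and if the real figure is lower, that result is weaker evidence than readers are led to believe.

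**Working it through.** **Inputs (Sample size section).** Difference 3 points; SD 8; correlation 0.7; two-sided 5%; 90% power; 75 per arm evaluable, 255/3 = 85 per arm enrolled.

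**Residual variance under ANCOVA.** 8² × (1 − 0.7²) = 64 × 0.51 = 32.64, a residual SD of 5.713.

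**Reproducing the stated figure.** n per arm = 2 × (z for alpha + z for power)² × 32.64 / 3².

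- Unadjusted 5%: 2 × (1.960 + 1.282)² × 32.64 / 9 = 76.2. This agrees with 75 to within rounding of the inputs. Power at 75 per arm is 89.5% by the normal approximation and 89.3% by the noncentral t with 3n − 5 = 220 degrees of freedom.
- Other readings do not give 75. A change-score analysis needs 90, the raw SD without baseline adjustment needs 150, and a one-sided 5% test needs 63.

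So 75 is a two-arm ANCOVA calculation with no correction for multiplicity.

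**Same formula at the corrected alpha.**

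- Two comparisons, 2.5% each: 2 × (2.241 + 1.282)² × 32.64 / 9 = 90.0 per arm (91 after rounding up).
- Three comparisons, 1.67% each: 2 × (2.394 + 1.282)² × 32.64 / 9 = 98.0 per arm (99 by the noncentral t).

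**Power of one experimental-versus-placebo comparison for a true 3-point difference (noncentral t).** The standard error is √(2 × 32.64 / 75) = 0.933 at 75 per arm and √(2 × 32.64 / 85) = 0.876 at 85.

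| Per-comparison alpha | 75 per arm | 85 per arm |
|---|---|---|
| 5% (as in the sample size) | 89.3% | 92.6% |
| 2.5% (two comparisons) | 83.0% | 87.8% |
| 1.67% (three comparisons) | 78.8% | 84.4% |

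**Difference detectable with 90% power at 1.67%.** (2.394 + 1.282) × 0.933 = 3.4 points at 75 per arm, and (2.394 + 1.282) × 0.876 = 3.2 points at 85 per arm. The noncentral t gives 3.45 and 3.24.

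**Omnibus three-arm F-test at 5%, 75 per arm.** Power is 92% if one arm lies 3 points from two equal arms, and 82% if the third arm lies midway between two arms 3 points apart.

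**The case against.** Four points can be made in the protocol's defence.

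*The family size is not stated.* The article never says that all three pairs are in the correction, and its trigger for subgroup analyses names only an experimental treatment against the reference. This stands as a qualification: with two comparisons the figure is 83.0%, not 78.8%, and the miss risk is 17%, not 21%. Three pairs is still the natural reading of unqualified pairwise comparisons among three arms, and neither reading gives 90%.

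*The omnibus ANCOVA may come first, at 5%.* A fair reading allows this, and its power can reach 92%. It does not show which regimen differs from placebo, its power falls to 82% in the midway case, and the figure of 75 comes from a two-arm formula.

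*If both regimens work, the trial will probably find at least one.* If both truly gain 3 points, at least one comparison with placebo is significant with about 91% probability under three-pair Bonferroni at 75 per arm, and both are with about 68%. The protocol states no at-least-one criterion, and if only one regimen works the per-comparison figure applies.

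*The analysis itself is sound.* This stands in full. Bonferroni is valid, type I error is controlled, and a detectable difference of 3.2 to 3.4 points lies within the 2-to-5-point range that the protocol quotes for clinical importance. The Discussion can also be read as including the active-versus-active contrast by design. The defect is confined to the power claim.

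The 30 additional patients do not answer the point. They are reserved for loss to follow-up, and power for each corrected comparison stays below 90% even if none is lost.

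**Conclusion.** The concern holds. The stated 90% belongs to an uncorrected two-arm comparison; the Bonferroni-corrected comparisons that answer the trial's question have about 79% power each at 75 per arm, and 84% if all 85 per arm are evaluable. These figures assume a family of three comparisons and the protocol's own difference, SD and correlation. With a family of two they become 83% and 88%. The validity of the analysis is not affected. What is wrong is the power figure for the primary endpoint, and with it the weight that a null result can bear.

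**What to change.** State in the Statistical analysis section which comparisons the Bonferroni correction covers, and correct the Sample size section to match. For three pairs, it could say that 75 evaluable patients per arm give about 79% power per pairwise comparison for a 3-point difference (84% with 85 per arm), or that 90% power applies to a difference of about 3.4 points (3.2 with 85 per arm). The cost is one corrected power statement and one sentence on multiplicity, with no extra patients; the stated power becomes less favourable.

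Two optional changes recover some power at the same sample size:

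- Limit the confirmatory family to the two comparisons with placebo, use Holm, and report active versus active descriptively. Power per comparison is then at least 83% at 75 per arm and 88% at 85. The price is that the active-versus-active contrast loses confirmatory status.
- Use the closed procedure valid for three arms: the omnibus ANCOVA at 5% and, only if it is significant, pairwise tests at 5%. By simulation, power is 82–87% at 75 per arm and 87–91% at 85, depending on where the third arm lies.

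Keeping three-pair Bonferroni with a true 90% would take 98 evaluable patients per arm, 294 in total. At the protocol's own retention of 225/255, that means enrolling 294 × 255/225 = 333.2, or 334 patients.

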## Discussion

The PLEASE study evaluates whether long-term antibiotic treatment of patients diagnosed with borreliosis-attributed persistent symptoms is efficient and leads to better patient outcome than short-term treatment. So far, there are few prospective, controlled data to support prolonged antibiotic treatment. Indeed, some studies have suggested positive outcomes on selected endpoints, such as persistent fatigue [17], cognitive functioning [29], quality of life [18], or clinical response rate [48], in specific groups of patients with putative persistent Lyme disease. However, these results were generally disappointing, and cannot be generalized. Other randomized clinical trials have not demonstrated beneficial effects of prolonged antibiotic treatment [10],[30]. Importantly, all of these studies were performed in North America. Borreliosis is caused by different *Borrelia* species in the US and Europe, with different clinical manifestations [49]. The present study will be the first randomized clinical trial to study long-term antibiotic treatment for borreliosis-attributed persistent symptoms in Europe.

The strategic choices leading to the design of a prospective, randomized, 3-arm study are complex. First, i.v. ceftriaxone followed by doxycycline is generally considered the gold standard therapy for complicated borreliosis [10]. Whereas administration of ceftriaxone for longer than 2 weeks has been advocated, a randomized, open-label study was unable to demonstrate that ceftriaxone treatment for 4 weeks would be significantly better [48].

Prolonged therapy with oral doxycycline has been associated with success in a large case series of patients with borreliosis-attributed persistent symptoms [50]. Data from another case series suggested that combined therapy with oral clarithromycin and hydroxychloroquine for at least 3 months may be at least as effective as prolonged doxycycline [51]. Hydroxychloroquine increases the lysosomal pH and is hypothesized to increase macrolide activity [52]. However, few conclusions can be drawn from those clinical studies, as they were retrospective, uncontrolled, observational studies. Based on these considerations, the present study was designed to compare a 12 weeks' course of doxycycline to 12 weeks of clarithromycin and hydroxychloroquine versus placebo.

To provide a standard treatment for all patients, and to cover potentially undiagnosed neuroborreliosis, all randomized patients receive an open-label course of i.v. ceftriaxone for 2 weeks preceding randomized blinded study drugs. In this respect, the present study differs from previous trials comparing prolonged therapy to placebo [10],[17],[18],[29]. By applying a standardized open-label treatment to patients in all treatment arms, the study is designed to compare short-term standard treatment [15] to prolonged therapy as advocated by several position papers [16],[53]. In addition, this approach does not leave potentially active infection untreated in patients who are randomized to the control arm, and it also controls for the wide variation in prior antibiotic therapies (or lack thereof) that patients with borreliosis-attributed persistent symptoms may have received.

As the primary outcome measure, we have chosen the physical component summary score (PCS) of the RAND-36 Health Status Inventory (RAND SF-36) [22]. The RAND SF-36 is similar to the Medical Outcomes Study (MOS) 36-item Short-Form General Health Survey (SF-36) [54]. The PCS, also known as the physical health composite score (PHC) [22], is computed by a non-orthogonal scoring algorithm. Several previous studies have used the alternate (SF-36) version of the PCS, applying a principal components analysis with orthogonal factors, with mental health components contributing negatively to this PCS score [54]. This SF-36 PCS has proven difficult to interpret as the level of mental health influences the physical health score and is therefore not purely a reflection of physical health. Furthermore, the SF-36 PCS is less sensitive to change than the underlying scales, while the RAND SF-36 PCS has been shown to be sensitive to change [55]-[62]. Despite the differences in calculation of both composite scores, they do correlate highly, indicating that they do represent similar constructs [58],[59].

In conclusion, the PLEASE study is expected to provide evidence for prescribing or withholding prolonged antibiotic treatment as compared to standard short-term treatment in patients with borreliosis-attributed persistent symptoms. In addition, this study may help to define subgroups of patients who may or may not benefit from additional antibiotic treatment, and contribute to a more cost-effective management of this disease entity.

